## Abstract

**Background:**

Parkinson’s disease (PD) is a neurodegenerative condition with progressive phosphorylated alpha-synuclein (P-SYN) deposition. Skin biopsies are a sensitive and specific source of tissue to detect intra-axonal P-SYN in patients with PD. Further, isolated REM sleep behavior disorder (iRBD) is a prodromal condition with a high risk of phenoconversion to PD. The objective of the Synuclein-Quantification (Syn-Q) study is to quantify cutaneous P-SYN across a range of PD severity and in iRBD and measure changes in P-SYN over time.

**Methods:**

After consent, participants with iRBD and PD across Hoehn and Yahr stages 1, 2, 3 will complete neurological and cognitive evaluation, motor and olfactory assessments, orthostatic vitals, and questionnaires. Skin biopsies (3 mm diameter and 3–4 mm depth) will be taken from distal leg 10 cm above the lateral malleolus, distal thigh 10 cm above the lateral knee, and posterior cervical region 3 cm lateral to the C-7 spinous process with quantitation of cutaneous intra-axonal P-SYN. Participants will return for follow-up visits to repeat study procedures at 6, 12, and 18 months following the baseline visit. This study is funded by the Michael J. Fox Foundation and is registered on Clinicaltrial.org (NCT06621602).

**Expected results:**

We anticipate that patients with more severe stages of PD will have higher levels of quantitative P-SYN. We also predict that increases in P-SYN over time will be associated with worsening disease severity.

**Discussion:**

In patients with PD, the detection and quantification of P-SYN is a critical step to supporting clinical trials that seek to alter the natural history of disease. Skin biopsies offer a more accessible, repeatable and quantifiable approach to monitoring phosphorylated alpha-synuclein compared to cerebrospinal fluid. This study will define the longitudinal rates of P-SYN change in patients with PD from prodromal to advanced disease.

**Clinical Trial Registration:**

https://clinicaltrials.gov/study/NCT06621602

## Introduction

Parkinson’s disease (PD) is a progressive neurodegenerative disorder with variable clinical phenotypes that include motor, autonomic and cognitive symptoms. The range of clinical features creates challenges to the early and accurate diagnosis of PD (1). Worldwide, over 11 million people are living with PD, and this is expected to increase to ~25 million people by 2050 (2) making it the most common movement-related neurodegenerative disorder (3). At autopsy, PD is pathologically characterized by the deposition of phosphorylated alpha-synuclein (P-SYN) within the central and peripheral nervous systems as aggregated proteins called Lewy bodies and Lewy neurites (4, 5).

Recently, the use of skin biopsies to detect peripheral Lewy neurites has bridged autopsy-level disease confirmation with an in-vivo diagnosis (6). Skin biopsy detection of P-SYN is one of several novel diagnostic advances in patients with PD (7–9). Skin biopsies have the advantage of being well-tolerated, relatively non-invasive and easily repeatable (10, 11). A recent prospective, blinded, cross-sectional multicenter study demonstrated over 92% sensitivity and over 96% specificity in detecting P-SYN from skin biopsies of patients with PD (10). The potential utility of P-SYN as a biomarker of disease holds broad applicability, ranging from improved clinical decision making, early detection and quantitation of change over time (12–14). Further, developments in early detection of PD could be bolstered by efforts to investigate P-SYN accumulation prodromal syndromes. Indeed, individuals with the prodromal syndrome isolated REM sleep behavior disorder (iRBD) have a high risk of phenoconversion to PD (15) and early detection and quantification of P-SYN in these individuals may better predict the likelihood of conversion to PD. In addition, the reliable quantification of cutaneous P-SYN has the potential to serve as a biomarker of target engagement in disease-modifying therapies.

The goals of the Synuclein-Quantification (Syn-Q) study are to (1) define rates of cutaneous P-SYN detection across a well-characterized group of patients with either prodromal iRBD or PD across a range of severities, (2) quantify the amount P-SYN detected from each of three biopsies to define the topographical distribution and, (3) measure rates of P-SYN change over time. Successful completion of this study will establish a foundational understanding of the natural progression of cutaneous P-SYN in patients with established or prodromal PD.

## Methods

### Study design and cohort

This is a multi-center, blinded, prospective, longitudinal, observational study to evaluate phosphorylated alpha synuclein pathology in cutaneous tissues in individuals with prodromal disease (iRBD) and PD across a range of disease (Hoehn and Yahr stage I, II & III). This study aims to enroll 75 subjects diagnosed with PD with 25 subjects enrolled in each Hoehn and Yahr stage (I, II, and III), totaling 75 participants (16). Their disease state will be assessed by the International Parkinson and Movement Disorders Society Unified Parkinson’s disease rating scale (MDS-UPDRS) completed at the baseline visit. Additionally, 25 subjects diagnosed with iRBD, confirmed by polysomnogram (PSG), without evidence of PD, will be included based on their medical history. A total of 100 subjects will be enrolled. Subjects will be evaluated at baseline, 6 months, 12 months, and 18 months (+/− 30-day window).

#### Inclusion criteria for PD cohort

Male and female 50–85 years of age.Confirmed diagnosis of PD by MDS clinical diagnostic criteria for Parkinson’s disease (17).Stage I, II, or III only as defined through the Hoehn & Yahr Scale in the OFF state which is a staging system measuring the progression and severity of PD symptoms (16). Stage I is defined as unilateral involvement only, Stage II is defined as Bilateral involvement without impairment of balance and Stage III is defined as mild to moderate bilateral disease, some postural instability, and physical independence. Mild–moderate stages were chosen for monitoring progression into more severe disease staging.

#### Inclusion criteria RBD cohort

Male and female 50–85 years of age.Confirmed diagnosis of iRBD confirmed by polysomnogram (PSG) (15); without symptoms of other neurodegenerative diseases.

#### Expert panel review

An expert panel of 2 movement disorder specialists and one neurologist with expertise in neurodegenerative disease will review all baseline and follow-up medical records, including inclusion criteria, questionnaires, structured examinations, and special investigations. Participants will be categorized or recategorized as iRBD, PD Stage I, PD Stage II, or PD Stage III (i.e., fulfilling diagnostic criteria with all information present or, if data are missing, as being highly probable to meet criteria for the specific diagnosis). Participants who do not fulfill diagnostic criteria for iRBD or PD will be categorized as indeterminate. Conclusions will be reached by consensus. Results of skin biopsies will be redacted from the medical records. In the event that this redaction is incomplete, the expert panel will not use skin biopsy results to form a diagnostic conclusion.

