#### Exclusion criteria for all subjects

Any history of a prior negative test for synuclein pathology in cerebrospinal fluid or skin.Clinical evidence of severe vascular disease (history of ulceration, poor wound healing, vascular claudication).History of allergic reaction to local anesthesia needed for skin biopsies.Use of blood thinners (aspirin or Plavix alone is allowed).Significantly impaired wound healing, history of scarring or keloid formation.Concurrently enrolled in a disease-modifying clinical trial.

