### Study visits and participant data collection

#### Trial synopsis

Approximately 25 sites will participate in recruiting 75 individuals diagnosed with Parkinson’s disease and 25 patients with iRBD in an 18-month longitudinal study where skin biopsies will be performed at 3 sites on each patient at 6-month intervals (baseline, 6, 12, and 18 months). Detailed quantified neurological examination, cognitive evaluation, medical history, and questionnaires will be performed at each visit. Additional biomarkers, imaging, and clinical information (if available) will be obtained for the purpose of determining disease progression for PD cohort and phenoconversion to clinically apparent synucleinopathy for the iRBD cohort. All testing will be repeated at all visits to define any changes to clinical diagnosis (clinical phenoconversion or progression). Skin biopsies will be repeated at the 6- and 12- and 18-month follow-up visits to determine the rate of P-SYN accumulation over time and the rates of nerve fiber degeneration within punch skin biopsies.

Study visit will include

Review of enrollment forms (inclusion and exclusion criteria).Informed consent.Review of medical history and current medications.Quantified neurologic examinations: All participants will have standardized neurologic examinations using published methods. The neurological examinations will be performed by the treating physicians. The specific examinations will include:

a MDS-UPDRS (Parts I, II, III & IV) (18).

Part III motor assessments will be performed in the “OFF” state, preferably with the last dose of Levodopa taken the night before. After conducting the MDS-UPDRS Part III, medication can be taken. (In order to reduce ‘OFF’ time for the participant, it is suggested that the MDS-UPDRS part III should be conducted as soon after consent as possible). The remainder of study visit would be conducted while patient is in the “ON” state. For those participants who are being treated with Deep Brain Stimulation, the stimulation will be turned off for the MDS-UPDRS part III assessment.

b Hoehn and Yahr scores.

5 Smell Testing: All subjects will complete the University of Pittsburgh Brief Smell Identification Test (BSIT) a 12-item, self-administered scratch and sniff test designed to measure olfactory function (19).6 Orthostatic vitals to be measured with the participant supine after 5 min and then standing after 3 min.7 Blood Plasma collection:

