c One 4 mL EDTA tube for genetic testing for inherited forms of PD (LRRK2, GBA1, PRKN, PINK1, and SNCA) which is collected at the baseline visit only.d One 10 mL EDTA tube collected at all visits for blood-based biomarkers (plasma p-tau-217, neurofilament light chain, glial fibrillary acidic protein). as exploratory outcomes.

8 Three millimeter diameter and 3–4 millimeter depth punch skin biopsies taken from the posterior cervical area 3 cm lateral to the C-7 spinous process, distal thigh 10 cm above the lateral knee, and distal leg 10 cm above the lateral malleolus after local analgesia with 1% lidocaine (9).9 Cognitive/Neurological Testing and Questionnaires: All participants will complete the following questionnaires/assessments:

e European Quality of Life Instrument (EQ-5D & VAS) (20)f SLUMS cognitive assessmentg Parkinson’s Disease Questionnaire-39 (PDQ-39) (21)h Orthostatic Hypotension Questionnaire (OHQ) (22)i REM sleep behavior disorder questionnaire (RBDSQ)j Scales for Outcomes in Parkinson’s Disease-Autonomic (SCOPA-AUT)k Geriatric Depression Scale-short form (GDS)

10 Collection of medical records for the last 3 years including any imaging (DaTscan, MRI, PET, SPECT, neurologic testing or genetic testing)

All assessments and blood collection will be repeated once every 6 months, with the exception of genetic testing which takes place only once at the baseline visit.

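### The expert panel's redaction rule covers skin biopsy results only, leaving other alpha-synuclein results in outside records visible to those who assign the diagnostic category

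*Protocol article*

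**What the plan says.** The Expert panel review section of the Protocol article sets up a three-member panel that "will review all baseline and follow-up medical records, including inclusion criteria, questionnaires, structured examinations, and special investigations". The panel places or re-places each participant as iRBD, PD stage I, II or III, or indeterminate. Full documentation is not required: a participant may be classified, "if data are missing, as being highly probable to meet criteria for the specific diagnosis".

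One blinding rule applies to the panel's files: "Results of skin biopsies will be redacted from the medical records". The fallback has the same scope: "In the event that this redaction is incomplete, the expert panel will not use skin biopsy results to form a diagnostic conclusion".

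Three other places bear on what those files contain:

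- **Trial synopsis, purpose of outside data:** "Additional biomarkers, imaging, and clinical information (if available) will be obtained for the purpose of determining disease progression for PD cohort". The same sentence gives phenoconversion as the purpose for the iRBD cohort.
- **Trial synopsis, records:** "Collection of medical records for the last 3 years". The Clinical data capture section adds that prior records and test results go into the electronic data capture system.
- **Exclusion criteria for all subjects:** "Any history of a prior negative test for synuclein pathology in cerebrospinal fluid or skin".

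**The concern.** The skin results are presumably withheld so that the clinical category is settled without knowledge of the quantity later analysed against it. A CSF or other alpha-synuclein result concerns the same underlying pathology, so the same reasoning applies to it. The rule does not reach it.

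The panel's categories match the groups for which the first primary objective reports P-SYN detection. Under Statistical considerations, phenoconversion or disease progression is the predictor in the repeated measures ANCOVA of P-SYN. If a positive synuclein result helps a doubtful case into a diagnostic category, the label and the biomarker share information. Assuming that such cases are also more often positive on skin biopsy, detection rates and the association between P-SYN and clinical status would look somewhat stronger than they are.

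This is not a detail left to a fuller document. The article states the redaction rule and draws it too narrowly.

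**Working it through.** The article gives no figure for this point, so the check is a comparison of the text.

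1. **What the panel sees.** It receives all baseline and follow-up records, with special investigations named. No type of record is held back except skin biopsy results.

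2. **Whether a CSF synuclein result can be in the file.** The study does not generate one: the Discussion lists the absence of parallel testing of other synuclein biomarkers as a limitation. Such a result could come only from outside care, through the three years of records or the additional biomarkers. The exclusion criterion allows that a candidate may have had a CSF test. The Study blinding section keeps clinical data apart from biopsy data, and an outside CSF result falls on the clinical side.

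3. **Direction of the information.** A prior negative CSF or skin test excludes. A definite CSF result from before enrolment in an enrolled participant is therefore positive. This does not hold for equivocal results, for tests in blood or other tissue, or for CSF tests done during follow-up, which may go either way.

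4. **Which calls it can affect.** PD requires MDS clinical diagnostic criteria and an OFF-state Hoehn and Yahr stage; iRBD requires polysomnography.
   - *Classified versus indeterminate:* this is the main exposure, above all where data are missing and high probability suffices.
   - *Phenoconversion:* the exposure is less direct. A result fixed before enrolment cannot show a change between visits. It could lower the threshold for a doubtful call, and a result obtained during follow-up could inform one.
   - *Stage I versus II versus III:* there is little exposure, because a uniformly positive result does not separate stages.

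5. **Whether the effect can be sized.** It depends on the share of participants with such a result and on the number of borderline calls. Neither is given. The share could be anywhere from 0% to 100%, so no estimate of bias is possible.

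6. **What one reclassified case does to a detection rate.** Suppose a group has 24 members, k of them P-SYN positive, and one positive case is moved in from indeterminate. The planned group size is 25.
   - Change = (k + 1)/25 − k/24 = (24 − k)/600.
   - k = 22 (22/24 = 91.7%, close to the PD positivity in Table 2): 2/600 = 0.3 percentage points, to 23/25 = 92.0%.
   - k = 12: 12/600 = 2 points, from 50% to 52%.
   - k = 0: 24/600 = 4 points.

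   At the PD positivity the article expects, one added positive case barely moves the rate. The article gives no detection rate for iRBD.

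**The case against.** The best case against the point is that exposure is inferred. CSF synuclein is not a study test, the examples in the records item do not name it, and an exclusion criterion says nothing about how often such tests occur. The categories are defined by clinical criteria and polysomnography, and phenoconversion means a clinically apparent synucleinopathy. Biopsy reading is blinded to study, visit and disease state, so the outcome side is protected. All of this stands, and it limits the size of the problem. It does not change the scope of the redaction rule or show that a CSF result would be withheld.

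A reader might also draw stronger conclusions that the document does not support:

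- *That each reclassified case shifts a group's rate by 1/25, or 4 points, upward.* The numerator and denominator move together, so 4 points arises only if none of the other 24 is positive. A shift near that size in a PD group would come from adding a P-SYN-negative case (22/24 = 91.7% to 22/25 = 88.0%), which lowers the rate.
- *That one or two panel decisions would decide the phenoconversion comparison.* This needs conversions to be few. The article gives no conversion rate and says only that the risk is high.
- *That a narrow redaction explains high detection rates.* Excluding people with prior negative tests enriches the cohort directly. That is a separate and probably larger effect, which wider redaction would not cure.
- *That any panel member who sees a result should step aside.* All three may have seen the same file, which could leave nobody to decide.

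**Conclusion.** The point holds in a limited form. The redaction and its fallback cover skin biopsy results only, while the panel sees all other records. Any other alpha-synuclein result there can inform borderline, missing-data and, less directly, phenoconversion calls. The category is then not fully independent of the P-SYN analysed against it.

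The bias cannot be quantified from the document and is probably small. That judgement rests on the clinical and polysomnographic definitions confining any influence to doubtful cases. The point also assumes that the panel's category is the one used in the analysis, which the matching group names suggest but the article does not state outright, and that at least some participants have an outside synuclein result. If none has, nothing is biased and the wording is merely incomplete. The change is still worth making because it costs so little.

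**What to change.** Reword the redaction sentence in Expert panel review, for example: *Before panel review, the results of every alpha-synuclein test (skin, CSF, blood or other tissue), whether obtained before enrolment or during follow-up, will be removed from the file.*

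Extend the fallback to the same tests and make it traceable: if a result is seen despite redaction, the panel does not use it, the exposure is logged by participant and visit, and the analyses that use the panel category are repeated without those cases as a sensitivity analysis.

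The redaction step already exists, and the PD and iRBD criteria as stated do not call for a synuclein test, so the panel loses nothing those criteria require. The cost is slightly more redaction work and one extra sensitivity analysis.

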#### Exclusion criteria for all subjects

Any history of a prior negative test for synuclein pathology in cerebrospinal fluid or skin.Clinical evidence of severe vascular disease (history of ulceration, poor wound healing, vascular claudication).History of allergic reaction to local anesthesia needed for skin biopsies.Use of blood thinners (aspirin or Plavix alone is allowed).Significantly impaired wound healing, history of scarring or keloid formation.Concurrently enrolled in a disease-modifying clinical trial.

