#### Definition of “positive biopsy results”

Only biopsies expressing P-SYN co-localized within a peripheral nerve axon (confirmed using immunostaining for anti-PGP9.5 and anti-P-SYN) will be considered positive. Any equivocal section will be considered negative. Any positive result indicates a positive case (e.g., if one of 3 biopsies is positive, the case is positive).

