### Objectives

This is a prospective longitudinal study of individuals with PD and prodromal RBD to establish cutaneous P-SYN deposition as a stable, reliable quantitative measure that changes in parallel with disease progression. The results of this study will provide the basis for establishing cutaneous P-SYN as a biomarker of response to disease-modifying therapeutic interventions and a possible surrogate biomarker for outcomes in clinical trials of disease-modifying therapies. The primary objectives of this study are:

To determine rates and patterns of P-SYN detection in iRBD and PD across Hoehn and Yahr stages I, II and III.To measure the change quantity and pattern of cutaneous P-SYN deposition over time.To enhance pathological detection and quantitation of P-SYN using rapid, high resolution, confocal microscopy combined with a novel AI-augmented pathology protein detection system.

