#### Statistical considerations

Descriptive statistics will be used to report all demographic information and clinical examination findings for all groups (PD stages I-III and iRBD). For continuous variables data will be reported as mean, standard deviation, median, minimum, maximum and inter-quartile range.

For the primary objectives, the presence or absence of P-SYN will be reported as a binary outcome for the first objective (detection of P-SYN). Quantitation of P-SYN will be measured as a continuous variable for the second objective (quantitation of P-SYN). We have established that a P-SYN > 0 is defined as a ‘P-SYN positive’ result and will separate groups using dichotomous measures. We will also investigate ROC curve analysis to determine if an alternative value would maximize sensitivity and specificity using continuous quantitative measurement of P-SYN. For comparisons over time, the initial biopsy results will be compared against future biopsy results using Krippendorff’s alpha reliability estimate. Reliability will be measured by quantified continuous P-SYN values between visits with the change in continuous values used to determine mean change over time. Additional endpoints will include change in disease severity over time, or phenoconversion to clinically apparent synucleinopathy (in patients with iRBD).

Data will be compared first using repeated measures Analysis of Covariance (ANCOVA), with phenoconversion/disease progression as the predictor variable. The primary dependent variable is the quantitative measure of P-SYN deposition. Other key covariates will include sex, cognitive examination scores, disease duration, UPDRS Part 2 and Part 3 total scores, and autonomic nerve fiber density (pilomotor nerve fiber density and sudomotor nerve fiber density) (32). These will be evaluated individually and together with descriptive and multivariate statistics to identify potential violations of statistical assumptions. If normality is violated, then transformations or bootstrap methods will be used. For comparisons of demographic and laboratory data within- and between groups, nonparametric tests (Kruskal–Wallis) will be used. The GEE (general estimating equation) method will be applied if the data cannot be transformed. All data will be presented as mean ± standard deviation and interquartile range using absolute values and change from baseline data for all tests of structure and function unless otherwise specified.

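### Excluding people with a prior negative synuclein test, while prior positives stay eligible, selects on an earlier measure of the objective 1 endpoint and biases all-participant detection rates upward by an unknown amount

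*Protocol article*

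**What the plan says.** Under Exclusion criteria for all subjects, the protocol article removes people with "Any history of a prior negative test for synuclein pathology in cerebrospinal fluid or skin". The criterion applies to the iRBD cohort and to all three PD stages.

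Entry is otherwise clinical. The PD cohort requires "Confirmed diagnosis of PD by MDS clinical diagnostic criteria for Parkinson’s disease" plus a Hoehn and Yahr stage, and the iRBD cohort requires polysomnographic confirmation. Neither inclusion list nor the exclusion list mentions a prior positive synuclein test, so such people remain eligible.

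The first primary objective (Objectives) is "To determine rates and patterns of P-SYN detection in iRBD and PD across Hoehn and Yahr stages I, II and III". The Introduction states the same goal: to "define rates of cutaneous P-SYN detection across a well-characterized group of patients". Statistical considerations makes it a binary outcome, and the case rule is that "Any positive result indicates a positive case", so one positive biopsy of three is enough.

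The limitations listed in the Discussion are the lack of controls, the 18-month follow-up and the absence of other synuclein biomarkers in parallel. Selection on prior test results is not among them, and no section restricts the detection rate to people without a known negative test.

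**The concern.** A detection rate is read as the share of people with a given clinical diagnosis in whom the biopsy finds P-SYN. If some people are kept out because the same test, or a related one, was already negative, likely negatives leave the denominator while likely positives stay. The rate in those enrolled is then not the rate in the clinical group.

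Prior testing is a realistic possibility. The Discussion describes skin biopsy and the spinal-fluid seed amplification assay as the most established tools now available, and the criterion has a purpose only if some candidates have been tested. With no controls enrolled and the selection not listed as a limitation, a reader would take the reported rates as applying to iRBD and PD patients in general.

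**Working it through.** **The one detection rate in the documents.** Table 2 prints 92.3% for PD, with 89 positive among 56 + 40 = 96 patients. Recomputed, 89/96 = 92.7%. The gap is immaterial here, and the printed 92.3% is used below. No detection rate is given for iRBD or for any single stage.

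**Model.** Let

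- p = true detection rate in the clinical group (92.3% from Table 2 for PD; 75% is an assumption, for a group with lower detection);
- f = share of candidates already tested (assumption; not in the documents);
- c = probability that the earlier test was negative in someone whose study biopsy would be negative (assumption);
- s = probability that the earlier test was negative in someone whose study biopsy would be positive (assumption).

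Removing everyone with an earlier negative result gives

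observed rate = p(1 − f·s) / [p(1 − f·s) + (1 − p)(1 − f·c)].

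**Direction.** If f = 0 or c = s, the expression reduces to p and there is no bias. If c > s, meaning that earlier and study results are positively associated, the observed rate exceeds p.

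**Worked cases at p = 92.3%.**

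- f = 50%, perfect agreement (c = 1, s = 0): 0.923 / (0.923 + 0.077 × 0.5) = 0.923 / 0.9615 = 96.0%, or +3.7 points.
- f = 10%, weak agreement (c = 0.5, s = 0.05): 0.923 × 0.995 = 0.9184 and 0.077 × 0.95 = 0.0732, so 0.9184 / 0.9915 = 92.6%, or +0.3 points.

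**Observed rates (%).**

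| True rate | f | c = 1, s = 0 | c = 0.8, s = 0.05 | c = 0.5, s = 0.05 |
|---|---|---|---|---|
| 92.3 | 10% | 93.0 | 92.8 | 92.6 |
| 92.3 | 25% | 94.1 | 93.7 | 93.1 |
| 92.3 | 50% | 96.0 | 95.1 | 94.0 |
| 92.3 | 100% | 100 | 98.3 | 95.8 |
| 75 | 25% | 80.0 | 78.7 | 77.2 |
| 75 | 50% | 85.7 | 83.0 | 79.6 |

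For PD with 10–50% tested, the bias is therefore +0.3 to +3.7 points, and it cannot exceed 100 − 92.3 = 7.7 points. For the assumed 75% group with 25–50% tested, it is +2.2 to +10.7 points.

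**Between-group differences.** Take true rates of 92.3% and 75%, a gap of 17.3 points, with perfect agreement.

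- f = 50% in both groups: 96.0 − 85.7 = 10.3 points, so the gap shrinks.
- f = 50% in the first group and 0 in the second: 96.0 − 75.0 = 21.0 points, so the gap widens.

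**Sampling error for comparison.** With 25 per group and a rate of 92.3%, the standard error is √(0.923 × 0.077 / 25) = 5.3 points.

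**The case against.** The strongest reply is that the effect may be negligible. The share previously tested is unknown. At 10% tested, the PD rate moves from 92.3% to at most 93.0%. At 25% tested with perfect agreement, the shift of 1.8 points is about a third of the 5.3-point standard error for a group of 25. This stands as a limit on size. It does not remove the bias, which is systematic and has a known direction, and only a record of prior testing can show that it is small.

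A second reply is that the criterion serves the longitudinal objective. Sample size justification allows for 5–10% biopsy-negative cases when sizing the analysis of change, so limiting their number is a sensible aim. The article does not give this reason, but it is plausible, and it is why removing the criterion would be a trade-off and not a plain correction. It does not make the objective 1 rate representative.

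Third, never-tested patients need not represent the clinical group either, because who gets tested is not random. That also stands, and it is a reason to show both rates and not only one.

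Two stronger readings are tempting. A reader might infer that the criterion compresses the comparison across stages. That needs similar prior testing in every group and a lower true rate in iRBD or stage I. The documents give neither, and with unequal testing the gap can widen. A reader might also infer that the 5–10% biopsy-negative allowance comes from Table 2 and is therefore wrong for this sample. The article states that allowance without a source, and fewer negatives than planned would only make it conservative.

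**Conclusion.** The point holds as a one-sided selection on an earlier measure of the objective 1 endpoint. As written, the all-participant detection rates are biased upward whenever some candidates were tested before and the results are positively associated. They are unbiased on this account only if no one was tested or the results are independent.

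The size cannot be taken from the documents. Under assumed testing shares of 10–50% and the three assumed levels of agreement, it is about +0.3 to +3.7 points for PD at a true rate of 92.3%, with a ceiling of about 8 points. For a group with an assumed true rate of 75% and 25–50% tested, it is about +2 to +11 points. The effect on differences between stages has no fixed direction. The documents do not support a claim that the rates are inflated by any particular amount, and nothing here touches the analysis of change over time.

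**What to change.** 1. Add a screening item that records prior synuclein testing: ever or never, type of test, and result. The planned "Collection of medical records for the last 3 years" cannot do this alone, because the criterion has no time limit and older tests would be missed. If the full protocol already records this, the item is in hand.
2. For objective 1, report detection by group in participants with no prior synuclein test, beside the all-participant rate. Show prior positives separately.
3. State with the results, and in the limitations, that the all-participant rate applies only to people without a known prior negative test.
4. The criterion and the full sample can stay for the longitudinal analysis.

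The cost is one data item, one extra denominator and wider intervals in the never-tested subset. As an illustration, 23/25 gives an exact 95% interval of 74–99%, and 14/15 gives 68–99.8%. The never-tested rate also needs the caveat that those never tested may differ from those tested.
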